##### 10.4.2 Factors affecting anemia

The following items are set as factors affecting anemia in this research.

Malignant tumors, hemorrhagic lesions, collagen disease, rheumatic disease, immunosuppressant or steroid use, other myelosuppressive factors

#### 11. Sample size and research period

##### 11.1 Sample size

The sample size is 2,000 patients.

##### 11.2 Research period

The patient registration period and follow-up end date are as follows.

Patient registration period: approval date–March 31, 2016

Observation period end date: 96 weeks after the start of the last registered patient (simultaneous outcome survey)

## 12. Definition of endpoints

### 12.1 Primary endpoints

#### 12.1.1 Renal function deterioration

Composite events of each event occurring 12 weeks after the start of treatment (see “10.4.1 Event – Renal function deterioration”) are set as renal function deterioration. The number of days until occurrence is calculated, with 12 weeks after the start of treatment as the starting point.

#### 12.1.2 CVD event

Composite events of each event occurring 12 weeks after the start of treatment are set as the CVD event. The number of days until occurrence is calculated, with 12 weeks after the start of treatment as the starting point.

### 12.2 Secondary endpoints

#### 12.2.1 eGFR decline rate

For each patient, the slope of the linear regression of all eGFR from the start of administration to the final eGFR observation time point on the number of measured days from the start of administration is set as the eGFR decline rate.

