### 4. Diagnostic criteria and disease stage / type classification

The diagnostic criteria and disease stage/type classification (definition) of the disease or condition specified in the eligibility criteria of this study are shown below.

Definition of chronic kidney disease

Defined as (i), (ii), or both are sustained for over three months.

(i) Renal damage revealed by abnormal urine, diagnostic imaging, blood, and pathology.

Proteinuria of over 0.15 g/gCr (albuminuria of over 30 mg/gCr) is particularly important

(ii)  $\text{GFR} < 60 \text{ mL/min/1.73 m}^2$

Calculation equation of estimated GFR (eGFR)

The estimated GFR (eGFR) is calculated using the following serum creatinine estimation equation (eGFRcreat):

$$\text{Male eGFR}_{\text{creat}}(\text{mL/min/1.73 m}^2) = 194 \times \text{Cr}^{-1.094} \times \text{age}^{-0.287}$$

$$\text{Female eGFR}_{\text{creat}}(\text{mL/min/1.73 m}^2) = 194 \times \text{Cr}^{-1.094} \times \text{age}^{-0.287} \times 0.739$$

Definition of renal anemia

1) Renal anemia is defined as anemia caused by a decrease in EPO production ability in the kidney due to renal damage.

2) Renal anemia includes a shortened red blood cell lifespan, decreased EPO response of hematopoietic cells, malnutrition, and in-circuit residual blood in HD patients.

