## 8.2 Discontinuation criteria for each patient and its handling

The necessary items are recorded up to the traceable time point in the case report form and the “discontinuation report form” in the following patients.

- 1) When a patient has died.
- 2) When a patient cannot be contacted and becomes untraceable.

However, if the transfer destination is known, the patient will be tracked by obtaining data from the transfer destination facility or by calling, and tracing will be continued.

- 3) When a patient requests discontinuation from research participation (patient information prior to discontinuation can be used).
- 4) When a patient has requested consent withdrawal (patient information after registration cannot be used).

- 5) When the lead principal physician or study physician deemed that research participation should be discontinued.

Patients in whom any of the following are applicable are not considered discontinued, with normal observation period inspections continued to the extent possible, and information up to the time point of 96 weeks collected.

- 1) Patients who transitioned to renal replacement therapy (dialysis, kidney transplantation).
- 2) When a patient has requested discontinuation of darbepoetin alfa use.
- 3) When the lead principal physician or study physician deemed that darbepoetin alfa use should be discontinued due to adverse events, etc.

The lead principal physician or study physician will make efforts to provide the best possible treatment to the patient even after discontinuation of research participation.

If it was determined after registration that a patient did not meet the eligibility criteria at the time of registration, then this will be considered “ineligible after registration,” and research participation will be concluded for the patient. Adverse event information up to 30 days after the decision to complete participation will be reported for patients in whom darbepoetin alfa was administered even once.

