| 6   | Blood test                                                  | Inspection date                                                                                                                                                                                                                                                       | yyyy/mm/dd                                                                                                                                                                |                                                                                                                                                                                                                                                                                                                                                                                                                                |
|     |                                                             | Inspection items                                                                                                                                                                                                                                                      | MCV, Hb (g/dL), serum Cr (mg/dL), eGFR (automatic calculation) (mL/min/1.73m  ), serum Alb (g/dL), serum iron (μg/dL), ferritin (ng/mL), TIBC or UIBC (μg/dL) |                                                                                                                                                                                                                                                                                                                                                                                                                                |

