#### 10.1.5 When discontinuing / withdrawing consent for participation in research

Provide answers within four weeks of discontinuation or consent withdrawal from research participation. Items from two onwards are not needed for patients who withdraw consent. Investigations during the normal observation period are continued if the patient can be traced even after the discontinuation of darbepoetin alfa administration or after event occurrence.

|    |                                                             |                                           |                                                                                                                                            |                                                                                                                                                                                                                                                                                                                                                                                                                                |
|----|-------------------------------------------------------------|-------------------------------------------|--------------------------------------------------------------------------------------------------------------------------------------------|--------------------------------------------------------------------------------------------------------------------------------------------------------------------------------------------------------------------------------------------------------------------------------------------------------------------------------------------------------------------------------------------------------------------------------|
| 1  | Research participation discontinuation / consent withdrawal | Discontinuation / consent withdrawal date | yyyy/mm/dd                                                                                                                                 |                                                                                                                                                                                                                                                                                                                                                                                                                                |

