### 13.3.2 eGFR decline rate

A linear mixed model, including the covariates shown in the previous sections, is applied to all the eGFR values from the start of administration to the final eGFR observation time point in order to search for factors that affect eGFR decline.

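### The eGFR decline analyses use values measured after dialysis or transplant, which usually flattens the slope after dialysis and can make it positive after transplant

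*Protocol*

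**What the plan says.** - **Endpoint.** Protocol 12.2.1 takes, for each patient, "the slope of the linear regression of all eGFR from the start of administration to the final eGFR observation time point", regressed on days since the start of administration.
- **Model.** In 13.3.2 a linear mixed model with covariates is "applied to all the eGFR values from the start of administration to the final eGFR observation time point". Neither section ends the series at renal replacement.
- **Follow-up after renal replacement.** Section 8.2 lists patients who move to dialysis or transplant among those not counted as discontinued, "with normal observation period inspections continued to the extent possible, and information up to the time point of 96 weeks collected". Section 10.1.5 adds that investigations "are continued if the patient can be traced even after the discontinuation of darbepoetin alfa administration or after event occurrence".
- **How eGFR arises.** The observation-period table in 10.1.3 includes serum creatinine and an automatically calculated eGFR, using the creatinine equation in section 4. A value is therefore produced whenever creatinine is entered, including on dialysis or with a graft.
- **Renal replacement is expected.** Maintenance dialysis and kidney transplantation are components of the primary renal composite (10.4.1). Section 5.2 excludes only renal replacement planned within 24 weeks of registration.

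**The concern.** Once dialysis has started, serum creatinine is partly set by dialysis clearance. After a transplant it is set by the graft. An eGFR computed from either says little about further decline of the patient's own kidneys, which is what a decline rate is meant to describe.

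The patients affected are those who reach kidney failure. One person can count as a renal failure under 12.1.1 and then contribute a slope under 12.2.1 that looks slower than it was, or even improving. The stated purpose of 13.3.2 is to find factors that affect decline. A factor that drives patients to renal replacement would have its association with decline weakened by the data that follow.

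**Working it through.** The protocol gives no expected slope, standard deviation or effect size for eGFR decline, so there is no figure of its own to reproduce on this point. The event count in 13.1 concerns the primary endpoints and is not used here.

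**Inputs from the protocol.** Visits at weeks 0, 2, 4, 6, 8, 10, 12, 16, 24, 36, 48, 60, 72, 84 and 96 (10.1.3), and the eGFR equation (section 4).

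**Assumptions.** Before replacement, eGFR = 12 − 6t, with t in years of 52.18 weeks. Replacement occurs at week 36, 48 or 60, and the visit in that week already counts as post-replacement. Computed eGFR on dialysis is 4, 5, 6 or 8; graft eGFR is 45. By the section 4 equation, a man of 65 with creatinine 8, 9 or 10 mg/dL has eGFR 6.0, 5.3 or 4.7; creatinine of about 11.6 gives 4 and about 6.2 gives 8.

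**Formula.** All-value slope = −6 + Σ(w − w̄)·d / Σ(w − w̄)². The first sum runs over post-replacement visits, and d is the recorded eGFR minus the value on the pre-replacement line. The mean visit week is w̄ = 478/15 = 31.87, and Σ(w − w̄)² = 29,852 − 478²/15 = 14,619.7.

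**Worked case (dialysis at week 36, eGFR 6).** At weeks 36, 48, 60, 72, 84 and 96, d = −1.86, −0.48, 0.90, 2.28, 3.66 and 5.04. The numerator is about 615. Then 615/14,619.7 × 52.18 = 2.20, so the slope is −6 + 2.20 = −3.80, a loss of 37%.

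**All cases (true slope −6.0 per year):**

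| Level after replacement | Week 36 | Week 48 | Week 60 | Decline lost |
|---|---|---|---|---|
| Dialysis, eGFR 4 | −5.27 | −5.21 | −5.07 | 12–16% |
| Dialysis, eGFR 5 | −4.54 | −4.49 | −4.41 | 24–27% |
| Dialysis, eGFR 6 | −3.80 | −3.78 | −3.75 | 37–38% |
| Dialysis, eGFR 8 | −2.34 | −2.34 | −2.43 | 60–61% |
| Graft, eGFR 45 | +24.7 | +24.2 | +21.9 | sign reversed |

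**Other trajectories.** A second set of fits let patients fall linearly from eGFR 12–30 to 6 at replacement.

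- Dialysis at weeks 24–48, with eGFR 4–8 afterwards: the all-value slope kept 13% to 78% of its true size and was never positive.
- Transplant at weeks 24–48, with graft eGFR 40–50: the slope was positive in every case.
- Week 72: effects were smaller. Starting at 12 with dialysis eGFR 4, the slope was −4.53 against a true −4.35, a slight reversal. Starting at 30 with graft eGFR 40, it stayed just negative, −0.71 against −17.39.

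**Mixed model.** One simulated data set of 600 patients was fitted per scenario, with random intercept and slope, 20–23% reaching renal replacement and a true group difference of −3.0 per year.

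| Share of replacements that are transplants | Cut at replacement | All values | Shrinkage |
|---|---|---|---|
| 0% | −3.09 | −2.54 | 1 − 2.54/3.09 = 18% |
| 5% | −2.98 | −2.32 | 22% |
| 10% | −2.72 | −2.18 | 20% |

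These are single runs, so only the direction and rough size should be read from them.

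**Precision after cutting.** With equal residual variance, the slope's standard error scales as 1/√Σ(w − w̄)². Cutting at week 36 leaves 9 values and a sum of squares of 448.9, so the ratio to the full schedule is √(14,619.7/448.9) = 5.71. Cutting at week 48 leaves 10 values and 1,099.6, giving 3.65.

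**The case against.** **The endpoint is secondary and exploratory.** The study tests no hypothesis, and its objective is an ESA response index related to renal and cardiovascular events. This stands and limits the severity, but it does not make the endpoint measure what it names.

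**The size depends on assumed levels.** This also stands. The documents give no eGFR after renal replacement and no frequency of dialysis or transplant. Inspections continue only as far as possible, so a complete post-dialysis series is the upper end. Late dialysis may matter little.

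**The SAP might restrict the data.** It could, but 13.3 leaves to the SAP the analyses not recorded in the protocol, and here the protocol itself records the span as all values.

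A reader might also infer three stronger things that the documents do not support:

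- *That fast progressors in general get positive slopes.* Dialysis alone produced none in any case run. A positive slope needs a transplant, whose frequency is not stated.
- *That the association with low ESA response is shown to be biased.* Section 13.3.2 uses the covariates of 13.3.1, which include Hb and darbepoetin dose but no response index or low-response class. That consequence is inference.
- *That the primary renal composite has the same fault.* Dialysis and transplant are events there, so later eGFR values matter little. At most they help confirm an earlier first point under the three-consecutive-points rule. Cutting them could move that event date later, so the eGFR components of the composite should stay as they are.

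**Conclusion.** The point holds for both 12.2.1 and 13.3.2. As written, the plan feeds values that do not reflect native kidney function into the decline analyses, and nothing in the protocol removes them. The sizes in the working are illustrations that rest on the assumed course before replacement, the assumed level after it, and complete visits to week 96. The loss is usually largest when replacement comes early after a fast decline. At cohort level, the secondary endpoint is pulled towards slower decline and associations with factors that drive kidney failure are weakened. The primary endpoints, and the ERI cut-off work built on them, are untouched. It should be fixed before analysis, but it is not critical to the study's main objective.

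**What to change.** Add one sentence to each of 12.2.1 and 13.3.2: only eGFR values measured before the onset date of maintenance dialysis or kidney transplantation are used. That date is already recorded with the renal events in 10.1.3, so no new data are needed and patient follow-up does not change.

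The cost is real. Individual slopes become much less precise for patients with early renal replacement: the standard error is about 5.7 times that of the full schedule for replacement at week 36, and 3.65 times for week 48. Stopping at renal replacement is also informative, because fast decliners stop first. Conclusions on decline should therefore rest on the mixed model already planned in 13.3.2, which handles unequal numbers of values, and not on an unweighted comparison of individual slopes. Add a joint model of eGFR slope and time to renal replacement as a sensitivity analysis.

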#### 12.2.2 Safety evaluation

The presence of adverse events and contents are evaluated for all adverse events occurring after the administration of darbepoetin alfa. MedDRA/J is used as a replacement dictionary for adverse events. The latest version at the time of analysis is used for the MedDRA/J. Those where the association with darbepoetin alfa is deemed “present” are defined as adverse drug reactions.

### 12.3 ERI

The following five indices are considered new candidates for the ESA response indices (ERIs) to be investigated.

- ERI-1A (index according to one time point at 12 weeks)

$$\frac{\text{DA administered dose 12 weeks after the start of treatment (}\mu\text{g)}}{\text{Hb concentration 12 weeks after the start of treatment (g/dL)} \times \text{weight 12 weeks after the start of treatment (kg)}}$$

- ERI-1B (index according to one time point at 12 weeks)

$$\frac{\text{DA administered dose 12 weeks after the start of treatment (}\mu\text{g)}}{\text{Hb concentration 12 weeks after the start of treatment (g/dL)}}$$

- ERI-2A (index that considers the cumulative administered dose up to 12 weeks and changes in Hb concentration)

$$\frac{\text{Total DA administered dose up to 12 weeks after the start of treatment } (\mu\text{g})}{\text{Amount of change} \times \text{weight at 12 weeks (kg)}}$$

- ERI-2B (index that considers the cumulative administered dose up to 12 weeks and changes in Hb concentration)

$$\frac{\text{Total DA administered dose up to 12 weeks after the start of treatment } (\mu\text{g})}{\text{Amount of change}}$$

- Change in Hb concentration (changes in Hb concentration up to 12 weeks)

$$\text{Hb concentration at 12 weeks (g/dL)} - \text{prior Hb concentration (g/dL)}$$

A similar index is created for the ERI index from the Hb concentration and darbepoetin alfa administered at 16 weeks and at 24 weeks in addition to that at 12 weeks, and the associations between these indices and event occurrence are also investigated. When the ERI index at 12 weeks favorably predicts event occurrence, then whether the ERI index composed of the values at week 10, 8, 6, 4, and 2 favorably predicted the event occurrence is confirmed in order.

New indices are further explored if no associations between these index candidates and renal function deterioration or CVD events were found.

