#### 【Dosage and administration】

- Initial dose

Adult: A usual adult dose of 30 µg of darbepoetin alfa (genetic recombination) per session is administered subcutaneously or intravenously once every two weeks.

- Maintenance dose

Adult: When improved effects are seen for anemia, a usual adult dose of 30–120 µg of darbepoetin alfa (genetic recombination) per session is administered subcutaneously or intravenously once every two weeks. When anemia improvement is maintained with an administration once every two weeks, then the starting dose is twice the dose at that time; dosing frequency is changed to once every four weeks, and 60–180 µg per session can be administered subcutaneously or intravenously once every four weeks.

The dose may be adjusted according to the extent of anemic symptoms, age, etc., but the maximum administered dose is set at 180 µg per session.

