**【When changing administration level】**

- 1) When changing the administration interval of this drug, shifts in the Hb concentration or hematocrit value will be sufficiently observed prior to extending the administration interval to confirm that stable shifts in the Hb concentration or hematocrit value are shown at the same administered dose. After doing so, change from once a week to once every two weeks, or once every two weeks to once every four weeks. Confirm shifts in the Hb concentration or hematocrit value after the change and adjust as appropriate.
- 2) Patients in whom the Hb concentration or hematocrit value did not reach the target range even after administering 180 µg per session should change the administered dose to 1/2 and change the administration frequency from once every two weeks to once every week, or once every four weeks to once every two weeks.

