### 13.2.2 Efficacy analysis set

The group excluding the following patients from the safety set is defined as the efficacy analysis set.

- Those who were ineligible after registration
- Those who discontinued darbepoetin alfa administration within 12 weeks after the start of treatment
- Those who do not have a single DA administration record 12 weeks after the start of treatment
- Hb concentration measurements are not obtained at the start of treatment and at 12 weeks

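### ERI-1A and ERI-1B take the dose without its interval, so the interval changes in the protocol's own dosing excerpt move the index the wrong way in patients who have switched

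*Protocol*

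**What the plan says.** Protocol 12.3 lists five candidate indices. The first is headed "ERI-1A (index according to one time point at 12 weeks"; its numerator is the "DA administered dose 12 weeks after the start of treatment" in µg, divided by week-12 Hb times week-12 weight. ERI-1B is the same without weight. No term for the interval between injections appears, and the unit is µg rather than µg per week. ERI-2A and ERI-2B, by contrast, use the "Total DA administered dose up to 12 weeks after the start of treatment". Section 12.3 also asks for similar indices at weeks 16 and 24 and, if week 12 predicts well, at weeks 10, 8, 6, 4 and 2.

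The package-insert excerpt in 8.1.2 gives the initial regimen: "A usual adult dose of 30 µg of darbepoetin alfa (genetic recombination) per session is administered subcutaneously or intravenously once every two weeks". It then describes two changes of interval. If improvement is maintained on 2-weekly dosing, "then the starting dose is twice the dose at that time; dosing frequency is changed to once every four weeks". Patients who miss the target range on 180 µg "should change the administered dose to 1/2 and change the administration frequency from once every two weeks to once every week", or correspondingly from every four weeks to every two. Doses rise one step at a time (30, 60, 90, 120, 180 µg), and 180 µg is the maximum per session.

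Section 13.3.1 sweeps a cut-off over the values of each ERI, compares time-dependent AUCs, and enters the week-12 dose as a covariate in the proportional hazards model.

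**The concern.** ERI-1 divides dose by Hb, so a high value is meant to flag a patient who needs much drug for little Hb. A dose per injection measures drug need only if everyone is injected equally often. The excerpt in 8.1.2 makes the interval depend on response: good responders move to larger, rarer injections, and patients failing at the top dose move to smaller, more frequent ones. Read as written, ERI-1 goes up in the first group and down in the second while the weekly dose stays the same. Two patients with the same Hb and weight on 120 µg, one every two weeks and one every four, also get the same ERI-1 although one receives twice the weekly dose.

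Finding a new ERI is the stated objective of the study. ERI-1 supplies two of the five candidates, and the week-12 results decide whether earlier weeks are examined.

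**Working it through.** The protocol gives no figure on this point, so there is none to reproduce. The check applies its formulas before and after each interval change.

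**Inputs**
- From 12.3: ERI-1B = D / Hb and ERI-1A = D / (Hb × W), with D the dose in µg.
- From 8.1.2: the dose steps, the 180 µg cap and the two interval changes.
- Added for comparison: weekly dose = D / I, with I the interval in weeks.
- Illustrative assumptions, not in the protocol: responder Hb 11 g/dL, non-responder Hb 9 g/dL, W = 60 kg for both. The ratios do not depend on these values.

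**Step 1: effect of each change, Hb and weight fixed**

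| Patient | Change | Weekly dose (µg) | ERI-1B | ERI-1A | Ratio |
|---|---|---|---|---|---|
| Responder | 30 µg every 2 wk → 60 µg every 4 wk | 15 → 15 | 2.73 → 5.45 | 0.045 → 0.091 | 2.0 |
| Responder | 60 µg every 2 wk → 120 µg every 4 wk | 30 → 30 | 5.45 → 10.91 | 0.091 → 0.182 | 2.0 |
| Responder | 90 µg every 2 wk → 180 µg every 4 wk | 45 → 45 | 8.18 → 16.36 | 0.136 → 0.273 | 2.0 |
| Responder, capped | 120 µg every 2 wk → 180 µg every 4 wk | 60 → 45 | 10.91 → 16.36 | 0.182 → 0.273 | 1.5 |
| Non-responder | 180 µg every 2 wk → 90 µg weekly | 90 → 90 | 20.0 → 10.0 | 0.333 → 0.167 | 0.5 |
| Non-responder | 180 µg every 4 wk → 90 µg every 2 wk | 45 → 45 | 20.0 → 10.0 | 0.333 → 0.167 | 0.5 |

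In the capped case the index rises by half while the weekly dose falls by a quarter.

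**Step 2: effect on ranking.** Take the responder on the 60 → 120 µg row and the non-responder on the 180 µg 2-weekly row.
- Before any switch: 0.333 / 0.091 = 3.67, non-responder higher.
- Only the responder has switched: 0.333 / 0.182 = 1.83. The order is right, but the ratio is halved.
- Both have switched: 0.167 against 0.182. The order is reversed, although the non-responder receives 90 / 30 = 3 times the weekly dose at a lower Hb.
- With weekly dose in the numerator: 90 / (9 × 60) = 0.167 against 30 / (11 × 60) = 0.045, ratio 3.67 whoever has switched.

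**Step 3: when the halving can occur.** From 30 µg there are four steps up to 180 µg.
- One step every 2 weeks: 180 µg at week 8, halving possible from week 10.
- One step every 4 weeks: 180 µg at week 16, halving from week 18.
- One step every 6 weeks: 180 µg at week 24, halving from week 26.

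A week-12 index therefore meets the halving only with near-fastest escalation, and a week-16 index only with escalation faster than one step every 4 weeks. A week-24 index meets it at one step every 4 weeks.

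**The case against.** The strongest reply is that little rests on ERI-1. Section 13.3 says there is no hypothesis to verify and sets no significance level. ERI-1A and ERI-1B are two of five candidates, ERI-2A and ERI-2B use cumulative dose, and the fifth index uses no dose. If none of the candidates is associated with events, 12.3 provides for new ones. This stands and lowers the severity: no primary endpoint and no sample-size figure depends on ERI-1.

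The reply on timing also stands. The excerpt asks for stable values at an unchanged dose before the interval is extended, and the halving is late for most plausible escalation speeds. The week-12 index will therefore be affected less than the later ones.

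A third reply is that 12.3 does not say that the dose is per injection, and that the statistical analysis plan may define a weekly dose. That is possible. But the µg unit, the one-time-point label and the contrast with the total dose in ERI-2 all point to a single dose. The protocol writes the formula out in full and nowhere corrects it for interval.

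**Conclusion.** The defect holds as a property of the formula. In patients who have changed interval by the index week, ERI-1 is multiplied by 2 (1.5 from 120 µg) in stable responders and by 0.5 in those not at target on 180 µg, with Hb and weight fixed. Both shifts run in the wrong direction. It should be corrected, mainly for week 24 and, where escalation is fast, week 16. It does not undermine the study as a whole. The result rests on reading the numerator as one injection's dose and on patients following the excerpt in 8.1.2.

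Three stronger conclusions that a reader might draw are not supported:
- **That AUCs and cut-offs for ERI-1 would reflect injection intervals rather than response.** The protocol gives no share of patients who have switched by any week, so the distortion is partial and of unknown size. The rank reversal needs both patients to have switched.
- **That the week-12 dose is chosen after the week-12 Hb is seen.** The schedule notes place the central blood draw before the injection, but nothing says that the dose is set on that day's Hb.
- **That 4-weekly patients leave the efficacy analysis set.** Section 13.2.2 excludes "Those who do not have a single DA administration record 12 weeks after the start of treatment". This can be read as no record from week 12 onward, which is how 12.1.1 uses the same time phrase for events. Section 10.1.3 also collects administrations from one survey point to the next, not only on the visit date.

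**What to change.** In 12.3, define the ERI-1 numerator as a weekly dose: the last DA dose given before the index Hb, divided by its dosing interval in weeks, both derived from the recorded administration dates and doses. For the earliest index weeks, such as 2 and 4, use total DA given before the index Hb divided by weeks since the start of treatment. On the initial regimen the two rules agree: 30 / 2 = 15 µg per week at week 2, and (30 + 30) / 4 = 15 at week 4. Use the same weekly dose for the week-12 dose covariate in 13.3.1.

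The text must say which recorded gap counts as the interval. With the gap before the injection, the first 120 µg dose after a switch would be scored as 120 / 2 = 60 µg per week instead of 30. With the gap after it, a fallback is needed when no further injection follows. A rule for irregular or withheld injections belongs in the same place.

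A fixed window such as weeks 8 to 12 divided by 4 is simpler but worse. It can catch zero, one or two 4-weekly injections as dates shift, and it cannot be formed at week 2.

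The cost is wording in 12.3 and 13.3.1 and some extra derivation work. Section 10.1.3 already collects the dates and doses, so no new data are needed, and no change to dosing is implied.
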